**Methods:**

A single-blinded randomized controlled trial will be conducted with 60 participants (n=30, 50% per intervention group) recruited from university and preuniversity counseling centers. The trial will measure whether the interventions reduce performance anxiety in students. Stratified randomization will be used to ensure equal distribution of baseline anxiety levels and gender across both groups. The primary outcome is a reduction in anxiety, measured using the State-Trait Anxiety Inventory-Y1 and State-Trait Anxiety Inventory-Y2 subscales. Secondary outcomes include emotional regulation and quality of life. Data will be collected at baseline, after the intervention, and during follow-up assessments. Statistical analyses will include parametric tests (eg, repeated-measures ANOVA and *t* tests) to compare anxiety reduction, emotional regulation, and quality of life across groups. The intention-to-treat approach will be applied to minimize bias due to participant dropouts. Sensitivity analyses will assess the robustness of the findings.

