## Methods

### Research Design

#### Overview

This study is structured as a parallel group randomized controlled trial (RCT) comparing 2 distinct interventions. It uses a stratified randomization approach to account for variations in baseline anxiety levels and gender.

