### Eligibility Criteria

#### Inclusion Criteria

According to the Romanian Youth Law Number 350 of July 21, 2006, our research targets the youth age group, which includes adolescents and young adults aged 14 to 35 years. Given that there are specific recommendations regarding participants being aged ≥15 years for using VR software and hardware programs, our program will include adolescents and young adults aged 16 to 35 years. Another essential criterion for inclusion in the research is diagnosis, that is, participants diagnosed with disorders within the anxiety spectrum of mental disorders, particularly performance anxiety, who are capable of understanding and providing consent to participate in the study. Participants lacking full decision-making capacity (eg, those with severe psychotic disorders, schizophrenia, or any other disorder affecting judgment and those who have attempted suicide) are not eligible for participation.

To be eligible, participants must present a clinical or subclinical level of anxiety symptoms, confirmed by medical or psychological evaluation. According to the *Diagnostic and Statistical Manual of Mental Disorders, Fifth Edition* and *the International Classification of Diseases, 11th Revision*, test anxiety can be included within the following broader anxiety disorders: generalized anxiety disorder, social anxiety disorder (SAD; social phobia), or specific phobia. Symptoms include worry on most days, for ≥6 months, related to numerous events such as academic performance, examinations, etc. Anxiety and worry are accompanied by at least 3 of the following symptoms: restlessness, fatigue, difficulty concentrating, irritability, muscle tension, and sleep disturbances. SAD involves fears or anxieties about one or more social situations in which the person is exposed to possible scrutiny by others. For students, this may involve oral examinations or class presentations. Social situations almost always provoke fear or anxiety and are avoided or endured with intense fear or anxiety. Regarding specific phobia, if it centers solely on examinations, then, depending on its intensity and duration, it may constitute a specific phobia. Generally, cases are recorded where fear or anxiety is excessive or disproportionate to the situation, as there is no real threat from the situation itself.

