### Sample Size Determination

Considering that the research aims to test and compare 2 types of interventions (VR-facilitated exposure and yoga techniques), using a small sample population allows a detailed initial analysis and a rigorous evaluation of the mechanisms involved without requiring significant resources or large samples. In the exploratory phase, this type of study can identify important preliminary trends and effects, which can later be validated through larger studies. The study involves continuous monitoring of anxiety and other psychological and neurobiological parameters, which requires considerable resources for each participant. A small sample enables closer and more detailed tracking of each participant, ensuring higher-quality data collection and avoiding uncontrolled variables. The proposed interventions, such as yoga techniques and VR exposure, are complex and require specific preparation for each participant. Thus, a smaller population allows for more efficient adaptation of the intervention to individual needs and optimal program implementation. In addition, studies of this type often require costly equipment and expertise, such as VR hardware and certified yoga instructors. Therefore, limiting the sample population allows for efficient use of available resources while maintaining intervention quality. Finally, it is worth noting that previous studies have shown that both yoga and VR interventions can yield significant results with a limited number of sessions and participants. This suggests that a small sample may be sufficient to detect the desired psychological effects in the initial phase. Considering power analysis, 30 participants per group are required to detect significant differences regarding anxiety reduction with 80% power at a 5% significance level.

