## Results

This study hypothesizes that the implementation of both VR techniques and yoga practices will yield a significant reduction in anxiety symptoms, as measured by the STAI-Y1 and STAI-Y2 scales. This study will start in the middle of the academic year in the fall of 2025 (to be relevant for performance anxiety) and will end in June 2026. It is anticipated that the VR group will experience a decrease in performance anxiety symptoms compared to the yoga group, which may require additional sessions. Concurrently, yoga sessions are expected to exert an intense impact with substantial psychoemotional rehabilitation effects. Furthermore, both interventions are predicted to lead to a meaningful enhancement in emotional regulation abilities, as assessed by the Emotion Regulation Questionnaire, with participants engaged in yoga anticipated to develop more effective cognitive reappraisal strategies. In assessing QoL, the use of the QoL Inventory among participants aims to reveal improvements, particularly in areas related to academic stress and examination-related anxiety, with both groups likely to report enhanced QoL after the intervention.

Comparative analyses between the 2 groups will highlight the specific outcomes associated with each technique. It is expected that the VR intervention may offer a more significant advantage in reducing acute anxiety symptoms, with rapid effects on stress perception. At the same time, the yoga group may sustain these effects over the long term by learning self-regulation methods. Neurobiological measurements are projected to provide evidence of favorable modifications in autonomic nervous system functioning, indicating beneficial biological responses to anxiety in both intervention groups. In addition, postintervention evaluations will reflect increased participant satisfaction with the techniques, particularly noting subjective differences in comfort and effectiveness. Yoga techniques are anticipated to be perceived as more relaxing, whereas VR may be seen as more stimulating.

In summary, the expected outcomes involve a reduction in anxiety symptoms, enhancement of life quality, and adaptation of emotional regulation strategies, underscoring the efficacy of both intervention methods in addressing performance anxiety among young individuals. This research may significantly contribute to the mental health field by providing relevant data for effective therapeutic strategies and new avenues of study.

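### With two active arms and no untreated arm, the plan cannot support its hypothesis and expected conclusion that both interventions work; only the VR-versus-yoga difference is randomised

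*Protocol article*

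**What the plan says.** **Design.** Under Research Design the article states: "This study is structured as a parallel group randomized controlled trial (RCT) comparing 2 distinct interventions". The Abstract gives 60 participants, 30 per arm. No untreated, waiting-list or attention arm is described anywhere.

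**Claims about each intervention.** The stated objective and goal are comparative, but other places go further:
- The Methods part of the Abstract says the trial will measure whether the interventions reduce anxiety.
- Results hypothesises that "both VR techniques and yoga practices will yield a significant reduction in anxiety symptoms, as measured by the STAI-Y1 and STAI-Y2 scales".
- The closing summary of Results describes the expected outcomes as "underscoring the efficacy of both intervention methods in addressing performance anxiety among young individuals".
- Anticipated Findings gives as an aim testing whether the two types of intervention improve mental health, and ends by repeating the hypothesis of significant reductions with both.
- Sample Size Determination uses easier detection of within-group effects as part of its case for a small sample.

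**Who enters.** Participant Recruitment draws from waiting lists for counselling or psychotherapy. Under Inclusion Criteria, "participants must present a clinical or subclinical level of anxiety symptoms", and Exclusion Criteria removes those with nonclinical anxiety. The STAI is completed before allocation, after each session and at the end of the programme.

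**The concern.** Whether each intervention works is a question about change against no treatment. With two active arms, the only evidence available is the before-after change within each arm. That change contains any treatment effect plus whatever would have happened anyway:
- regression to the mean in people chosen because their anxiety is raised;
- natural course in people who have just sought help;
- the timing of exams in the academic year;
- repeated completion of the same scale.

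The design cannot separate these parts. The article does not mention them as rival explanations and does not limit its conclusion to the comparison between arms. At stake is a published claim that both interventions are effective, in an article whose Future Directions section foresees implementing both, when the data could look much the same if neither had any effect.

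**Working it through.** **1. The plan's own figure.** The article states that "30 participants per group are required to detect significant differences regarding anxiety reduction with 80% power at a 5% significance level". It gives no effect size or SD, so the figure can only be solved backwards. With a two-sided 5% test (assumed), the detectable between-arm difference is (1.960 + 0.842) × √(2/30) = 0.72 SD, or 0.74 SD with the t distribution. A paired test within one arm of 30 reaches 80% power at a standardised change (mean change divided by SD of change) of 0.53. Within-arm falls are therefore easier to make significant than the randomised contrast.

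**2. Assumptions.** The documents give neither a STAI cutoff nor a retest correlation. I assumed a standard normal score, selection above the 50th, 70th or 84th percentile (q), retest correlation r from 0.5 to 0.9, no treatment effect, 30 per arm, and a paired t test at two-sided 5% counting only falls (nominal rate 2.5%). Each cell has 20,000 simulated trials.

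**3. Selection on the baseline score itself.** The expected fall is (1 − r) × λ, where λ is the mean of the truncated normal: 0.80, 1.16 and 1.52 SD at the three cutoffs.

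One cell by hand, q = 0.70 and r = 0.7:
- cutoff 0.524, λ = 0.348/0.30 = 1.159
- expected fall 0.3 × 1.159 = 0.348 SD
- variance of the truncated score 1 + 0.524 × 1.159 − 1.159² = 0.264
- variance of change 0.3² × 0.264 + (1 − 0.7²) = 0.534, so SD 0.731
- standardised change 0.348/0.731 = 0.476

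The paired test has 56% power at 0.4 and 75% at 0.5, which agrees with the simulated 72%.

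Chance of a significant fall in one arm with no treatment effect:

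| Cutoff | r = 0.5 | 0.6 | 0.7 | 0.8 | 0.9 |
|---|---|---|---|---|---|
| 50th percentile | 64% | 52% | 41% | 28% | 16% |
| 70th percentile | 92% | 85% | 72% | 53% | 29% |
| 84th percentile | 99% | 98% | 91% | 76% | 46% |

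**4. Screening separate from the baseline STAI.**
- If every pair of occasions has the same correlation, baseline and final score have the same expected value, rλ. The expected fall is zero and the rate stays at the nominal 2.5%.
- If correlation decays with time, the expected fall is r(1 − r)λ. The rate is 14% to 61% over the same cutoffs and r from 0.5 to 0.9.

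**5. Natural course alone.** A spontaneous fall with standardised change 0.3 is significant in 36% of arms, and one of 0.5 in 75%.

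**6. Both arms together.** Under selection on baseline, both arms are significant in 8% (50th percentile, r = 0.8), 28% (50th, 0.6), 28% (70th, 0.8), 71% (70th, 0.6) and 83% (84th, 0.7) of trials. These are close to the squares of the single-arm rates, for example 0.53² = 0.28.

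**7. The randomised contrast.** In the same five cells the between-arm test keeps a type I error of about 5%. Both arms regress alike, so the difference is not biased.

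**The case against.** The strongest reply is that the conclusion about both methods is a forecast in a protocol article, not an analysis rule. The objective and goal are comparative, the analysis section speaks of comparing groups, and no paired test within arms is specified. This is fair as to the closing sentence. But Results labels the reduction with both as a hypothesis, Anticipated Findings makes it an aim, and the sample size section leans on within-group effects. An analysis plan, if one exists, cannot supply a missing control arm.

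The second reply concerns size, and much of it stands. No STAI cutoff is stated, eligibility rests on diagnosis and on medical or psychological evaluation, and Screening sends the test set only to people who already meet the criteria. That order suggests selection before the baseline STAI, where the rate may be as low as nominal. Trait anxiety, which the article describes as enduring, should regress less than state anxiety. One eligible diagnosis requires worry over at least 6 months, so a transient peak at entry cannot be assumed for everyone. Exam timing has no fixed direction either: rising pressure over a programme of 2 to 4 weeks would hide falls.

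A reader might infer more than the documents support:
- **That the trial will report both as effective whether or not either works.** Both arms would have to be significant together, which happened in 8% to 83% of trials in the cells examined, and the Dissemination Policy commits to reporting whatever the outcome.
- **That a non-significant arm difference will be read as equal efficacy.** No section plans this. The goal, Results and Anticipated Findings all predict differences between the arms.

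**Conclusion.** The point holds as one about what the design can show. Two randomised active arms identify the VR-versus-yoga difference and nothing about either intervention against no treatment, so the hypothesis and expected conclusion about both exceed the design. This part needs no assumed figure.

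The size is uncertain. With no treatment effect, one arm of 30 would show a significant fall in 2.5% of trials (separate screening, equal correlations), 14–61% (separate screening, decaying correlation) or 16–99% (selection on baseline, r from 0.9 down to 0.5). All three rest on assumed cutoffs and correlations. The claim that regression to the mean alone would often produce significance is therefore conditional on how screening works. The comparison between arms is unaffected.

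**What to change.** In the Methods part of the Abstract, in Results and in Anticipated Findings (its opening aim and its closing summary), replace the hypothesis of a significant reduction with both interventions, and the conclusion that both are efficacious, with a statement that:
- confirmatory inference rests on the between-arm difference in STAI-Y1 and STAI-Y2, each with its 95% CI;
- within-arm changes (time effects) are reported descriptively and are not interpreted as evidence of efficacy.

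Time effects from a repeated-measures model can still be shown; only their reading changes. A claim that each intervention works would need an untreated or waiting-list arm, which is a different trial. The cost is wording only, and the trial claims less.

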## Discussion

### Anticipated Findings

This study aims to test whether 2 types of psychological interventions could significantly improve mental health for young people. First, we expect that implementing VR techniques will significantly reduce anxiety symptoms soon after starting the program, and second, we expect that yoga practices could have long-term significant benefits. These hypotheses align with previous research findings indicating short- and long-term benefits for mental health. Research has shown that both VR and yoga can effectively reduce anxiety symptoms.

For example, VR interventions and particularly those based on CBT have been widely recognized as an effective treatment for anxiety disorders, including performance anxiety. Wu et al [42] indicated that VR-assisted CBT significantly decreases anxiety symptoms compared to traditional methods. Other studies focusing on specific types of anxiety (eg, social anxiety) indicated that VR-CBT effectively reduced anxiety levels in patients with generalized SAD, allowing them to practice social interactions in a safe environment [36]. In addition, exposure-based CBT, which is a core component of VR-CBT, has been validated as the gold standard for treating anxiety disorders, including performance anxiety [43]. This method involves gradual exposure to anxiety-provoking situations, which is facilitated by the virtual environment, making it less intimidating for patients [44]. In conclusion, virtual therapy using cognitive behavioral techniques presents a robust approach for managing performance anxiety. The combination of VR-CBT’s immersive exposure methods and cognitive restructuring strategies offers a comprehensive framework for addressing the cognitive and behavioral aspects of anxiety. As digital health solutions continue to evolve, the integration of VR in therapeutic settings holds significant promise for enhancing the accessibility and effectiveness of mental health interventions.

Yoga-based psychoemotional support intervention provides a holistic approach to managing emotions and stress. According to studies, breathing techniques and yoga poses can contribute to a significant reduction in stress and anxiety levels, thus improving QoL. According to Brown and Ryan [45], mindfulness cultivated through meditation, a central component of yoga, can reduce anxiety and enhance overall life satisfaction. Research by Cramer et al [7] has shown that regular participation in yoga classes is associated with a significant reduction in depressive and anxiety symptoms. This highlights that yoga practice not only improves physical health through poses and breathing techniques but also plays an essential role in enhancing emotional health.

Controlled breathing, known as pranayama, is a central element in yoga practice, with beneficial effects on the autonomic nervous system. According to Jerath et al [46], slow pranayamic breathing techniques induce a physiological response that promotes the activation of the parasympathetic nervous system, associated with states of relaxation and regeneration. Deliberately manipulating the breath generates a hyperpolarization current in the nervous system, facilitating a state of calm and reducing emotional reactivity. Melnychuk et al [47] investigated the connection between breathing and attention, concluding that controlled breathing positively influences cortical functioning and neurophysiological balance. This discovery is essential for understanding the mechanisms by which yoga and pranayama can improve mental well-being and help effectively manage stress.

Yoga practice impacts not only psychological health but also neurological health. Măgurianu and Măgurianu [48] presented the hypothesis that breathing techniques can stimulate processes of angiogenesis and neurogenesis, thus promoting neuronal regeneration. In neuroscience, the law by Hebb states, “neurons that fire together, wire together.” This explains how constant yoga practice, by repeatedly activating the neural groups responsible for well-being states, can facilitate the formation of durable neural networks, thus contributing to brain regeneration and improved cognitive functioning.

By applying the basic principles of Yama and Niyama, combined with techniques of asana (poses), pranayama (controlled breathing), and meditation, yoga offers a practical set of tools for emotion management and stress reduction. Its benefits are not only limited to mental health but also include positive influences on physiological and neurological functioning. These techniques, although accessible to any practitioner, offer significant benefits only in the context of continuous commitment and disciplined practice. Integrating these principles into psychoemotional interventions can yield valuable results in reducing anxiety and improving QoL, demonstrating the holistic potential of yoga as a method of balancing mind and body.

Regarding the effectiveness of yoga practices for anxiety performance, these practices have been associated with significant reductions in anxiety, as they promote relaxation and mindfulness, which are crucial for managing stress [49]. The comparative effectiveness of these interventions suggests that while VR may offer immediate relief, yoga’s benefits may accrue over time, necessitating multiple sessions for optimal results [49]. Both interventions are anticipated to enhance emotional regulation abilities, particularly through the development of cognitive reappraisal strategies. Cognitive reappraisal, a strategy that involves changing one’s interpretation of a situation to alter its emotional impact, has been linked to improved emotional outcomes [50,51]. Studies indicate that individuals who engage in yoga practice report using cognitive reappraisal more frequently, which can lead to better emotional management in stressful situations [52]. Furthermore, the neurobiological mechanisms underlying cognitive reappraisal have been extensively studied, revealing that this strategy activates brain regions associated with emotional regulation, such as the prefrontal cortex [50]. This suggests that participants in both the VR and yoga groups may experience enhanced emotional regulation capabilities after the intervention. In summary, the implementation of both VR techniques and yoga practices is hypothesized to yield significant reductions in anxiety symptoms, enhance emotional regulation abilities, and improve overall QoL. The evidence suggests that while VR may provide immediate relief, yoga’s long-term benefits are substantial, particularly in fostering effective cognitive reappraisal strategies. Future research should continue to explore these interventions’ comparative effectiveness and their underlying mechanisms to optimize therapeutic approaches for anxiety management.

### Future Directions

The results from this study can facilitate the implementation of VR-CBT and yoga intervention to address performance anxiety in students. Through a standardized framework for comparing the 2 interventions, we hope to add value to the expanding field of digital and integrative mental health therapies. As anxiety is increasingly common in young adults, particularly those within academic settings, our research could guide targeted therapeutic approaches that are tailored to a specific person’s needs and preferences.

More generally, this research highlights the need for new, accessible forms of mental health support. VR-CBT is an emerging digital mental health intervention, and it enables individuals to access and explore anxiety in virtual, safe environments. The integration of cognitive restructuring techniques within virtual therapy further enhances its efficacy. Cognitive restructuring helps individuals identify and modify negative thought patterns that contribute to their anxiety. By combining these techniques with VR, patients can visualize and interact with their fears, which has been shown to foster cognitive change and reduce anxiety. For instance, a study highlighted the effectiveness of VR-CBT in helping participants confront and alter their automatic negative thoughts through immersive experiences [53]. Finally, the convenience and accessibility of digital platforms for delivering CBT are crucial in addressing the barriers many individuals face in accessing traditional therapy. Internet-based CBT programs have been shown to significantly reduce psychological distress among patients with anxiety disorders, making them a viable alternative for those unable to attend in-person sessions [54]. This is particularly relevant in the context of the COVID-19 pandemic, where many individuals experienced heightened anxiety levels and barriers to traditional mental health services [55].

In contrast, yoga is a more conventional, all-encompassing discipline that enhances mental health through physiological and psychological processes that may have long-term effects. Finally, our findings could help design individualized mental health programs; VR-CBT might be delivered for people who require instantaneous anxiety relief, and yoga would support long-term emotional stability and health. Future research should address larger, more varied samples or apply these interventions to broader therapeutic contexts to further explore their synergy.

